### The train-the-trainer approach

Two 4-hour sessions of the train-the-trainer workshops will be provided for front-line healthcare providers participating in the study. The workshop a) covers the developmental characteristics, medical issues and special needs in ASD children, b) discusses the basic concepts, training skills and safety issues of exercise training for children with ASD, after which c) the details of the 16-week exercise training program will be introduced. Steps for running the exercises and using the exercise equipment correctly will be demonstrated by professional trainers. The workshop also involves a trial run of the exercises among the participants. We further prepare a manual that provides information on the method and training goals, exercise and visual tools, safety concerns, and guidelines for adjusting the difficulty levels of each exercise to current physical fitness levels of the participants. In addition, five physical and psychosocial components including muscle strength, coordination, endurance, social skills, and following instruction should also be evaluated and plotted on a radar chart for each exercise item (Fig. 2). This information will facilitate front-line health care providers to select and plan for their exercise training sessions for their group of children. Each training class will be conducted by three front-line healthcare providers with a group of 7 to 8 children in each community center. A professional coach and an exercise specialist in our research team will visit each center biweekly during the 16-week training period to observe the progress of the training classes and provide feedback to the front-line healthcare providers for the progression of the training sessions.

**Fig. 2 Fig2:**
[figure not shown]
An example of the radar charts showing the progression of the rope skipping exercise from the beginning stage (simple, play by themselves) to the final stage (complex, needs interaction with other children)

### Ethics

The study protocol has been approved by the Human Research Ethics Committee of the Education University of Hong Kong (Ref. No.: 2016-2017-0223). All the participants will join the research on a voluntary basis. After an introductory presentation at each community center, an information fact sheet and a consent form will be distributed to the front-line healthcare providers and parents. The completed consent form will be collected by the research team before the study commences. Consent to publish will also be obtained from parents that information obtained from this research may be used in future research and may be published, however, the personal details of each child will not be revealed; videotape or photos of the training sessions may be taken which will be used for teaching or presentation purpose, however, children’s’ faces will be blurred on the videos / photos and cannot be recognized.

### Measurements

#### Symptoms of ASD

##### The Childhood Autism Spectrum Test (CAST)

Previously known as the Childhood Asperger Syndrome Test, is a 37-item parental questionnaire to screen for Autism Spectrum Disorders [28]. The cut-off score is 15 for possible ASD or related social-communication difficulties.

##### The Autism Spectrum Quotient-Children’s Version (AQ-Child)

Is a parent-report questionnaire to quantify autistic traits [29]. There are five subscales. A Chinese version was developed in 2008 [30].

#### Children’s physical fitness

Children’s physical fitness will be assessed by a battery of tests: the PREFIT battery [31], which comprises the measurements of body weight and height and waist circumference to assess anthropometry, the PREFIT 20 meter shuttle run test [32] for cardiorespiratory fitness, handgrip strength and standing long jump tests for muscular strength of upper limbs and lower limbs respectively, 4 x 10 meter shuttle run test for speed-agility and one-leg stance test for balance [31]. In addition, the upper limb power [33] of each child will be assessed.

##### Anthropometric

Standing height without shoes will be measured using a seca 217 stable stadiometer to the nearest 0.1 cm. Body weight will be measured using a portable Tanita scale (Model BF-522; Tanita Corporation, Tokyo, Japan). Waist circumference is taken as the mean of two readings of the minimum circumference between the umbilicus and xiphoid process.

##### ***PREFIT 20 meter shuttle run test*** [32]

In this test, children run back and forth between 2 parallel lines 20 meters apart concurrently with an audio signal. The test finishes when the child failed to reach the end lines concurrent with the audio signal on two consecutive occasions or when the child stops because of exhaustion. Because of the young age of the preschoolers, adaptations of the original test will be made by decreasing the initial speed and by having two evaluators running with a reduced group of children in order to provide an adequate pace [31]. Test results will be expressed as the number of laps completed.

##### Handgrip strength

Each child will be given a brief demonstration and verbal instructions for the handgrip strength test using the Takei T.K.K.5001 GRIP-A handgrip dynamometer (Takei Scientific Instruments Co. Ltd, Tokyo, Japan). The dynamometer will be adjusted according to the child’s hand size. The test will be done in the standing position, with the wrist in the neutral position and the elbow extended. Children will be given verbal encouragement to ‘squeeze as hard as possible’ and apply maximal effort for at least 2 seconds. Two trials will be allowed alternately with both hands. The best value (kg) of the two trials for each hand will be chosen, and the average of both hands will be recorded [31, 34].

##### Standing broad jump

After demonstration, the child will be instructed to stand with his/her feet at the shoulder’s width, and toes just behind the take-off line. When ready, he/she bends the knees with swing both arms, then push off vigorously and jump as far as possible. The distance is measured from the take-off line to the point where the back of the heel nearest to the take-off line lands on the ground [35]. Three jumps are allowed and the best of these attempts will be recorded [31].

##### 4 x 10 meter shuttle run

Two parallel lines 10 meters apart will be marked on the floor using marking tape. Children will be instructed to run and turn as fast as possible between the two lines. The test covers a distance of 40 meters. The best of two attempts will be recorded in seconds [31].

##### One-leg stance test

In this tests, the child stands on one foot with the supporting leg on the floor and the free leg flexed at the knee, maintaining the balance position as long as possible. The test ends when the child cannot maintain the required position. The test will be done once with each leg and the mean time (seconds) will be used in the analysis [31].

##### Overhand throw

When ready, the child uses the preferred arm to complete an overarm throw of a bean bag (140 grams). Three trials are allowed and the furthest distance for the throw will be recorded in centimeters [33].

#### Children’s nonverbal intelligence, socio-emotional skills and cognitive-linguistic skills

##### The Standard Raven’s Progressive Matrices (SRPM)

This is a test of nonverbal reasoning ability [36]. The Standard Raven’s Progressive Matrices (SRPM) consists of 60 patterned diagrams with a missing part to be identified. The *SRPM is norm-referenced in Hong Kong*. This test will be used to estimate nonverbal ability among our participants.

##### The Chinese version of the Psychoeducational Profile, Third Edition (CPEP-3)

The CPEP-3 assesses skills and behaviors in children with ASD [37]. We will administer the social reciprocity and affective expression subtests. *The Psychoeducational Profile-Revised (PEP-R)* has been previously translated into Chinese and a validation study done in Hong Kong to examine the psychometric properties [38]. The current Chinese PEP-3 edition is also well validated and will be used in this study [39].

##### Joint attention task

The assessment of joint attention for socio-emotional skills will be performed under supervision of the experimenter. A series of tasks will be conducted within a time span of 25 minutes. The tasks are based on earlier developed tasks to provoke checking, gazing, pointing, follow pointing and joint visual attention of the child [40].

##### The face and eye tests

The ability to read facial expressions and eyes for the understanding of emotion is assessed by the *Face and Eye tests* developed by a team of researchers from the Autism Research Centre, University of Cambridge [41, 42]. The two tests have been widely used for assessing children with autism spectrum condition.

*The Faces Test* is a 20-item test on simple emotions and complex mental states [41]. Originally, the photos were taken with a western model. As our project takes place in Hong Kong where all our participants are Chinese, a Chinese model was recruited to pose the same facial expressions. The photographs were displayed digitally with the corresponding emotion or mental state word below the photo. The translation of those emotions was completed by independent translators and all discrepancies were resolved by consensus.

*The Eyes Test* is a 28-item test with photos of different sets of eyes belonging to different people [42]. The test is designed to examine social intelligence by investigating how well an individual can identify the photographed person’s feelings or thoughts. This is more challenging than the Faces Test, as participants have to choose among four options provided, the feelings and thoughts are more implicit, and the eyes are the only available clue to determining the person’s emotion.

##### Recognition of facial emotions

For the facial emotion recognition task, eight faces are chosen for each of the six basic emotions from the JAFFE database [43]. Children view the faces on the computer screen and are asked to choose which emotion the face is portraying from a list of the six basic emotions that appear alongside the picture.

##### Cantonese Oral Language Deficiency Early Identification Test for Pre-primary Children (CEIT)

The CEIT is the second locally published standardized language screening test [44]. The contents of the test are mainly selected from the curriculum adopted in Po Leung Kuk kindergartens with additional reference to two local studies on oral language development in preschool children [45, 46]. The test contains 11 sections, which measure a wide range of expressive language knowledge, including vocabulary (nouns, verbs, adjectives, super-ordinates and classifiers), sentence structures (active sentence, passive sentence, comparative sentence, double object construction and relative clauses) and narrative. There are between two and six items in each section and a total of 49 items altogether. Section 1 to 5 (24 items) are selected for use in this study. The test adopts a dichotomized scoring method (i.e. correct and incorrect responses) and children scoring below -1 SD for age are considered to fail the screening [47].

##### Motor automaticity

This test will be administered to assess children’s cognitive-linguistic skills. In the single-task motor automaticity condition, the finger-tapping task and the stepping task will be applied. The finger-tapping task will be adopted from a digital finger-tapping test[48]. Children will be instructed to tap as many times as possible with their index finger of the preferred hand within one minute. The frequency of taps will be recorded. In the stepping task, children are instructed to step on a mini exercise stepper for as many times as possible within one minute. The frequency of steps within one minute will be recorded. In the dual-task coordination, children will be asked to tap as many times as possible with the index finger of their preferred hand while simultaneously stepping on the stepper. The frequency of steps and finger-taps in one minute will be recorded [49, 50].

##### Children’s Color Trails Test (CCTT)

CCTT will be employed as a 2-dimensional paper and pen assessment of visual attention and cognitive flexibility in this study. It is typically used to assess sustained and divided visual attention, sequencing, cognitive flexibility and inhibition [51, 52].

##### M&M (Unexpected contents) false belief test

This test will be administered to assess the first- and second-order Theory of Mind abilities of the children. In the "Unexpected contents" or "Smarties" task, experimenters ask children what they believe to be the contents of a box that looks as though it holds the candy "Smarties". After the child guesses (usually) "Smarties", it will be demonstrated to the childthat the box in fact contains pencils. The experimenter then re-closes the box and asks the child what he/she thinks another person, who has not been shown the true contents of the box, will think is inside. The child passes the task if he/she responds that another person will think that "Smarties" exist in the box, but fails the task if he/she responds pencils [53].

#### Adaptive functioning in real-life situations

##### The Adaptive Behavior Assessment System, Second Edition (ABAS-II)

Will be used to assess adaptive skills where ratings are provided by parents, teachers and caregivers [54]. It is widely used to evaluate independent and social functioning among individuals with ASD. The rating scale measures 10 adaptive behavior skills, including Communication, Community Use, Functional Academics, Health and Safety, Home or School Living, Leisure, Self-Care, Self-Direction, Social, and Motor Skills. In our project, we focus on five of those rating scales, namely communication, community use, leisure, self-direction and social skills.

#### Children’s adherence to the training program

Children’s adherence to this exercise training program will be monitored by their attendance rate of the 16-week training sessions (32 sessions) and their performance record in each session. The performance record for each child will be recorded by the front-line healthcare providers, which includes the items of (1) exercise items the child performed; (2) how many circuits the child finishes in a session; (3) the Borg Rating of Perceived Excretion (RPE) by each child [55]; (4) appearance of physical signs of vigorous exercise (shortness of breath, sweating, face flushing) in each child.

#### Coaching efficacy of the front-line healthcare providers (trainers)

An 8-item adherence score is developed to assess the coaching efficacy of the trainers. The assessment items include whether the trainers (1) can apply simple and direct instruction; (2) have provided visual assisted instruction; (3) have demonstrated the activities; (4) have provided encouragement in the form of small gifts such as stickers; (5) have provided verbal positive reinforcement; (6) completed performance record for children; (7) are able to adjust the tasks accordingly based on the ability of the child; and (8) are able to adjust the tasks accordingly based on the interests of the child (i.e. follow the child’s lead). The adherence score of each trainer will be scored by a professional coach in our research team during his/her visit to the training sessions at the first session and the last session of the program.

#### Evaluation on global functioning improvement of children by their parents

The Clinical Global Impression scale on Improvement (CGI-I) evaluates change from the initiation of treatment on a seven-point scale from 1=very much improved since the initiation of treatment to 7=very much worse since the imitation of treatment [56]. The CGI-I reported by parents or caretaker will be used for evaluating children’s global functioning improvement in three aspects, namely social and communication skills, attention and behaviour and motor functioning.

### Statistical methods

Raw data of all key variables will be tested for normality prior to analysis. Analyses will be done using repeated-measures Analysis of Variance (ANOVA) and mixed models as the primary design. Multiple imputations will be used for missing observations at post-intervention and 3-month follow-up. Reporting of the results of the study will be in accordance with the CONSORT 2010 Statement [59].

In the aforementioned analysis plan it is assumed that children will play the game individually and the data will not be clustered. However, in cases of clustered data due to the formation of groups in which several children play the game in the same room, the analyses will be conducted in MPLUS 6.11 [60].

First, the two groups will be compared with respect to age, gender, nonverbal intelligence (IQ), and CAST and AQ-Child severity score in order to assess the comparability between them with independent samples t-tests. Baseline descriptors that differ significantly are taken into account in the following analyses.

To investigate the effectiveness of the TTT program, we explore both within-subject effects (changes within children across time) and between-subject effects (changes between children in the control condition versus the intervention condition). ‘Time’ is the within-subject variable, with three levels: T1 (baseline), T2 (effect), and T3 (follow-up). ‘Condition’ is the between-subject variable, with two levels: intervention condition and control condition. The tasks we employed will all yield continuous data. We corrected for multiple testing using Bonferroni correction. Statistical analyses are performed using SPSS 24.0 statistical software (SPSS) and are two-tailed, with a level of significance of α = 0.05.

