**Method:**

Using a randomized controlled trial design, the effectiveness of the game-based exercise program will be examined for 112 young children with ASD. These children were randomly assigned to two groups, which will be tested and trained in either one of the two arms of the waitlist conditions (control and intervention). The assessment of physical and psychological traits will be conducted at baseline (pre-test), at 16-weeks (post-treatment) and at 32-weeks (follow-up) of the program.

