### Aims and hypotheses

The first aim of this study was to test the effectiveness of a supervised game-based exercise training program in promoting motor skills and physical fitness, as well as reducing stereotypical and maladaptive behaviours in preschool children with ASD. These physical abilities served as the primary outcomes, while social and language skills were measured as secondary outcomes. Secondly, this study also aimed to evaluate the efficacy of this program as implemented by front-line healthcare providers through the train-the-trainer approach. We hypothesized that when compared to the waitlist control group, the exercise training program will lead to (1) increased motor skills and physical fitness and reduced stereotypical and maladaptive behaviours in preschool children with ASD; thus providing evidence for (2) the feasibility and sustainability of this supervised tailor-made exercise training program for young children with ASD following the train-the-trainer approach.

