## Methods/Design

### Study design

This is a randomized controlled trial (RCT) study registered with the Chinese Clinical Trial Registry (ChiCTR-IOR-17011898). The study is ongoing and is during the subject recruitment phase (August to Sept, 2017). Community centers within a local non-government organization were recruited. The recruited ASD children will be randomly assigned to either the treatment group or a wait-list control group using the *simple randomization* method with the employment of a toolbox provided in MS Excel, to be performed by the first author. The exercise training program will be offered to children in the wait-list control group after the posttest of the treatment group (Fig. 1).

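### Each outcome's own baseline score is modelled only as a level of Time, so the T1-to-T2 group effect is a difference in raw change: valid, but less precise than a baseline-adjusted comparison

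*Protocol article*

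**What the plan says.** The Statistical methods section of the protocol article names the model: "Analyses will be done using repeated-measures Analysis of Variance (ANOVA) and mixed models as the primary design". It then sets out the two factors: "Time’ is the within-subject variable, with three levels: T1 (baseline), T2 (effect), and T3 (follow-up" and "Condition’ is the between-subject variable, with two levels: intervention condition and control condition". Baseline is thus one of the repeated responses. Nothing says that the two arms share a common baseline mean.

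Covariates are dealt with separately: "the two groups will be compared with respect to age, gender, nonverbal intelligence (IQ), and CAST and AQ-Child severity score", followed by "Baseline descriptors that differ significantly are taken into account in the following analyses". No fitness, motor, social or language score is on that list.

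The baseline scores will exist. The abstract says "The assessment of physical and psychological traits will be conducted at baseline (pre-test), at 16-weeks (post-treatment) and at 32-weeks (follow-up) of the program", and Aims and hypotheses gives the physical measures primary status: "These physical abilities served as the primary outcomes, while social and language skills were measured as secondary outcomes". Under Study design, children "will be randomly assigned to either the treatment group or a wait-list control group using the *simple randomization* method", and no stratification or balancing is mentioned.

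**The concern.** In a randomized trial the two arms have the same expected baseline. A model that gives each arm its own free T1 mean ignores this. On complete data its T1-to-T2 interaction subtracts the whole observed baseline difference from the T2 difference. Because rho is below 1, only part of a chance baseline difference carries over to T2, so full subtraction over-corrects and adds noise. Adjusting for the T1 score subtracts only the part that carries over.

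What is at stake is precision on the primary fitness tests, with data that the trial already plans to collect. The point does not depend on how the five descriptors are chosen, or on whether T3 stays in the model.

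**Working it through.** **Inputs from the Sample size calculation section:** 50 evaluable children per arm, 80% power, two-sided alpha 0.05, planned difference 0.90 SD.

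**Assumptions:** the T1-to-T2 correlation rho, which the documents do not give, is shown from 0.3 to 0.8. T1 and T2 variances are taken as equal (SD = 1) unless stated.

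**1. The plan's own figure.** A two-sample t-test for 0.90 SD at 80% power and two-sided 0.05 needs 21 per arm (20.4 before rounding up), not 50. With 50 per arm, an outcome of SD 1 has 99.4% power at 0.90 SD and 80% power at 0.566 SD. The mismatch is a separate matter. It is why both effects are used below.

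**2. Variances.**
- Raw change: 2(1 − rho).
- T2 adjusted for T1, or T1 means constrained equal: 1 − rho².
- Ratio, adjusted to change: (1 − rho²) / [2(1 − rho)] = (1 + rho)/2.
- Standard error of the group effect: sqrt(2 × variance / 50).

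| rho | Variance, change | Variance, adjusted | Ratio | SE, change | SE, adjusted |
|---|---|---|---|---|---|
| 0.3 | 1.40 | 0.91 | 0.65 | 0.237 | 0.191 |
| 0.5 | 1.00 | 0.75 | 0.75 | 0.200 | 0.173 |
| 0.7 | 0.60 | 0.51 | 0.85 | 0.155 | 0.143 |
| 0.8 | 0.40 | 0.36 | 0.90 | 0.126 | 0.120 |

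A simulation with 50 per arm and 20,000 replicates gave change-to-adjusted ratios of 1.52, 1.33 and 1.16 at rho 0.3, 0.5 and 0.7, against 1.54, 1.33 and 1.18 from the formula.

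**3. Power at a fixed effect** (noncentral t, 50 per arm, standardized effect = difference / sqrt(variance), alpha 0.05).

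| rho | 0.566 SD: change | 0.566 SD: adjusted | 0.90 SD: change | 0.90 SD: adjusted |
|---|---|---|---|---|
| 0.3 | 66% | 84% | 96.5% | 99.7% |
| 0.5 | 80% | 90% | 99.4% | 99.9% |
| 0.7 | 95% | 97.5% | above 99.9% | above 99.9% |
| 0.8 | 99.3% | 99.7% | above 99.9% | above 99.9% |

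The plan also applies a Bonferroni correction without giving the divisor. If it were 7 (an assumption), power at 0.90 SD would be 85.1% vs 97.4% at rho 0.3 and 95.8% vs 99.2% at rho 0.5.

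**4. Unequal variances.** If the T2 SD is k times the T1 SD, the change variance is 1 + k² − 2·rho·k and the adjusted variance is k²(1 − rho²). With k = 1.2 (an assumption) and rho 0.5 these are 1.24 and 1.08, a ratio of 0.87 instead of 0.75. At rho 0.7 and 0.8 the ratios are 0.97 and 0.997.

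**5. Chance imbalance.** The SE of a baseline difference is sqrt(2/50) = 0.20 SD. Given a baseline difference D, the change estimate shifts by −(1 − rho)D. For D = 0.20 and rho 0.5 that is 0.10 SD in the opposite direction; the adjusted estimate does not shift. This is the same loss as in step 2: the squared SEs differ by 0.0400 − 0.0300 = 0.0100 = 0.10².

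**The case against.** The strongest reply is that nothing in the planned analysis is invalid. The difference in change is unbiased over randomizations and its type I error is sound, so the complaint is only that a more efficient model exists. This stands, and it limits the point to efficiency.

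Second, the article says mixed models, and a mixed model can carry a common baseline mean. The descriptor list serves a comparability check and does not expressly forbid other terms. A reader might infer that the plan rules out baseline adjustment; it does not go that far. But the section does state a model, with T1 as a level of Time crossed with Condition, and repeated-measures ANOVA, which it also names, does not impose equal baseline means. The point therefore concerns the stated model, not a detail left to another document.

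Third, at the protocol's own 0.90 SD and alpha 0.05 there is almost nothing to gain unless rho is low. This also stands. The primary tests are mostly best-of or averaged performances in children aged 4 to 6, so a rho above 0.5 is plausible. On the other side, the 0.90 SD comes from a social skill training study, whereas the primary outcomes are physical, so a smaller true effect cannot be excluded.

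Fourth, taking T1 out of the response altogether would conflict with the stated wish to explore change within children. That is correct, and the fix below keeps that analysis.

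**Conclusion.** The point holds as a loss of precision. On the model as written, the T1-to-T2 group effect is a difference in raw change, and under equal variances its variance exceeds that of the adjusted comparison for every rho below 1. The loss is material at 0.566 SD when rho is about 0.5 or lower (10 points of power at 0.5, 18 at 0.3). It is small at 0.7 (2.4 points) and negligible at 0.8. At 0.90 SD it is about 3 points at rho 0.3 and under 1 point at 0.5 or above, with alpha 0.05. All of this rests on an assumed rho and on equal variances, and the gain shrinks if the T2 SD exceeds the T1 SD.

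Two stronger readings are not supported. A reader might infer that simple randomization makes the result biased. It does not: chance imbalance is the source of the lost precision, through over-correction conditional on the imbalance, and is not a second harm. A reader might also infer that the trial is underpowered for its planned effect because of this choice. At 0.90 SD and alpha 0.05, the change analysis keeps at least 96% power for every rho considered. The change is worth making because it costs almost nothing.

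**What to change.** For every continuous outcome measured at T1, use one of two forms:

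- Keep T1, T2 and T3 as responses in the mixed model, constrain the T1 mean to be equal in the two arms, and report the resulting T2 difference as the group effect. This keeps the within-child description in the same model.
- Or compare T2 between arms with the outcome's own T1 score as a prespecified covariate, and keep within-child change as a descriptive analysis.

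Apply the chosen form to all such outcomes, whether or not the arms differ on them at baseline. The CGI-I rates change directly and has no T1 score, so it falls outside this change.

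The cost is a few sentences in the Statistical methods section and one or two degrees of freedom per outcome. The T1 scores are already scheduled, and no further children, visits or measurements are needed.

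### The effectiveness analysis pools T3, when waitlist children are expected to have had the programme, with T2, the only treated-versus-waitlist visit, and does not say which effect tests efficacy

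*Protocol article*

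**What the plan says.** Under Statistical methods, the model is introduced as follows: "Analyses will be done using repeated-measures Analysis of Variance (ANOVA) and mixed models as the primary design". Time "is the within-subject variable, with three levels: T1 (baseline), T2 (effect), and T3 (follow-up", and Condition "is the between-subject variable, with two levels: intervention condition and control condition". To judge effectiveness, the authors write that "we explore both within-subject effects (changes within children across time", together with "between-subject effects (changes between children in the control condition versus the intervention condition". The section names no Time by Condition term and no between-arm contrast at T2, and it does not say that exposure changes in the control arm between T2 and T3.

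The design sections describe that change. Study design states: "The exercise training program will be offered to children in the wait-list control group after the posttest of the treatment group". Intervention gives the programme a length of 16 weeks. The Abstract places the later assessments "at 16-weeks (post-treatment) and at 32-weeks (follow-up) of the program", whereas Statistical methods calls the last visit something else: "Multiple imputations will be used for missing observations at post-intervention and 3-month follow-up".

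Aims and hypotheses frames the question as a comparison with the waitlist group, and Sample size calculation plans on a treated-versus-untreated difference of 0.90 SD.

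**The concern.** A waitlist design gives a randomised treated-versus-untreated comparison only until the waitlist is released. Here that is T2. At T3 the comparison is between children whose programme ended about 16 weeks earlier and children who are expected to have just completed it.

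Neither effect named in the text isolates T2:

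- The within-subject effect is change over time in children aged 4 to 6. It includes growth and practice on the tests, and no control is set against it.
- The between-subject effect, in the usual repeated-measures ANOVA sense, is the Condition main effect. It averages the arm difference over all three visits. If the programme works and its benefit lasts, controls catch up by T3 and this average shrinks, so success can look like a weak effect.

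At stake is whether the reported test and estimate answer the randomised question.

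**Working it through.** **1. Exposure by visit** (Abstract, Study design, Intervention; controls assumed to start promptly after T2)

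- T1, week 0: neither arm treated.
- T2, week 16: intervention arm has finished; controls untreated.
- T3, week 32: intervention arm finished 16 weeks ago; controls have had 32 − 16 = 16 weeks, the full programme.
- If T3 is instead 3 months (about 13 weeks) after T2, it falls near week 29, with controls about 13 of 16 weeks in. The interval from week 16 to week 32 is 112 days, or 3.7 months. On either timing T3 is not treated versus untreated.

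**2. The plan's own figure.** For 0.90 SD, 80% power and two-sided α = 0.05, the requirement is 20 per arm (normal approximation) or 21 (t test), not the stated 50. With 50 per arm, 0.90 SD has 99% power at a single visit, and 80% power corresponds to d = 0.566 SD. That mismatch is a separate matter. Both effect sizes are carried below, with n = 50 per arm.

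**3. Assumptions not in the document.** Unit SD at each visit; equal correlation r between visits of 0.3, 0.5 or 0.7; no arm difference at T1. Arm differences at (T1, T2, T3) are (0, d, 0) for full catch-up, (0, d, d/2) if half the gap remains, and (0, d, d) with no crossover.

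**4. Formulas**

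- Condition main effect: mean of the three differences, with the SD of a child's three-visit mean = √((1+2r)/3). Noncentrality = √(50/2) × mean/SD. Example, full catch-up, d = 0.566, r = 0.5: mean 0.566/3 = 0.189, SD 0.816, noncentrality 5 × 0.189/0.816 = 1.16, power 21%.
- Time by Condition interaction: F with 2 and 196 df, λ = (50/2) × (sum of squared deviations of the three differences from their mean)/(1 − r). Same example: 25 × (2/3 × 0.320)/0.5 = 10.7, power 84%.
- T2 adjusted for T1: residual SD √(1 − r²). Same example: noncentrality 5 × 0.566/0.866 = 3.27, power 90%.

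**5. Results** (power in %, r = 0.3 / 0.5 / 0.7)

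| Test | Estimates | d = 0.566 | d = 0.90 |
|---|---|---|---|
| Condition main effect, full catch-up | d/3 | 25 / 21 / 18 | 53 / 44 / 38 |
| Condition main effect, half gap left | d/2 | 48 / 40 / 35 | 86 / 78 / 70 |
| Condition main effect, no crossover | 2d/3 | 72 / 63 / 55 | 98 / 95 / 91 |
| Interaction, full catch-up | no single effect | 69 / 84 / 97 | 98 / >99 / >99 |
| Interaction, half gap left | no single effect | 56 / 71 / 91 | 93 to >99 |
| T2 adjusted for T1 | d | 84 / 90 / 98 | >99 |

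**6. Reading the table.** Two things dilute the main effect. Averaging in T1 takes it from d to 2d/3 even without crossover; full catch-up takes it on to d/3. The interaction's λ is the same for (0, d, 0) and (0, d, d), because both have squared deviations summing to 2d²/3. The omnibus test therefore cannot tell controls catching up from an effect that persists against untreated controls.

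**The case against.** A reader might infer that the planned tests cannot estimate the treatment effect, or that the trial is badly underpowered because of them. The document does not support that.

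- The words about changes between children in the two conditions can be read as a loosely worded Time by Condition comparison. The section never says that a Condition main effect decides effectiveness. On the interaction reading most of the power loss disappears: 93% or more at the plan's own 0.90 SD, for full catch-up or half the gap remaining.
- T2 already carries a label marking it as the effect visit, and T3 is labelled as follow-up.
- Mixed models are already planned, and a T1-to-T2 contrast can be taken from them. An analysis plan that is not shown may specify it.
- Study design says only that controls will be offered the programme. Start date and uptake are not given in the text, and the flow chart is not visible here. Completion by T3 is an expectation, and every catch-up fraction is an assumption.

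All of this stands, and it limits the point. It does not remove it. The section does more than leave detail open: it fixes the factor levels and names the effects by which effectiveness is judged, and neither effect is the T2 comparison that the hypothesis needs. The interaction reading rescues power but still gives no estimate of the treatment effect, and it responds to what controls do while being treated.

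**Conclusion.** The point holds as a fault in how the efficacy test is specified. The analysis text mixes the one treated-versus-waitlist visit with a visit at which both arms are expected to have had the programme.

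The size depends on the reading. As a Condition main effect, the test estimates d/3 under full catch-up, at a severe cost in power. As an interaction, its power at 0.566 SD is 56–97% across the two catch-up assumptions, and the remaining fault lies in what the test estimates. The within-child Time effect is uncontrolled on any reading.

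The exposure pattern follows from the document's own schedule if controls start promptly and take up the offer. The power figures rest on the assumed correlations and catch-up. The data as planned can yield the right estimate. The conflict between week 32 and a 3-month follow-up is a smaller, separate inconsistency; T3 lacks an untreated comparator under either.

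**What to change.** In Statistical methods:

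- Name as the primary efficacy test the between-arm difference at T2 (week 16), adjusted for the T1 value of the same outcome, for example from the mixed model already planned.
- Take T3 out of the efficacy test. Report it as descriptive: maintenance in the intervention arm, and T2-to-T3 change in the waitlist arm.
- State that neither the Condition main effect nor within-arm change over time will be interpreted as efficacy.
- Reconcile the timing of T3 between the Abstract and Statistical methods.

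The cost is analysis wording only. The visits are already planned, and Study design describes the trial as still recruiting, so the change can be made before outcome data are compared. The price is that the controlled claim is limited to week 16, which is all that the waitlist design can support.
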